### Participants

To participate in the study, subjects had to be willing and able to provide and sign both written Informed Consent and Health Insurance Portability and Accountability Act Authorization (HIPAA) forms for this study, undergo bronchoscopy and phlebotomy procedures for the collection of biological specimens and follow up interviews and CT scans. Entry criteria required subjects to be at high demographic risk for lung cancer based on age 50–90 years, and a minimum of 20 pack-years of cigarette smoking history, but to have low likelihood for lung cancer at the time of bronchoscopy. Both current (defined as self-reported regular use of cigarettes) and former cigarette smokers were eligible. Consent included bronchial brush biopsy to obtain NBEC samples at time of either a) standard of care (SOC) bronchoscopy for a clinical indication for bronchoscopy, b) a study-driven (SD) bronchoscopy, or c) bronchoscopy done for another research study to which they had consented (also considered to be SD). Subjects had to be without a diagnosis of lung cancer prior to or at enrollment. Women with the potential for pregnancy had to have a negative result on a pregnancy test. Subjects were excluded if they were previously diagnosed or treated for lung cancer or had a high pretest likelihood of lung cancer, if they were positive for hepatitis B, C, HIV, or had active TB or if the physician deemed them to be medically inappropriate due to safety concerns. Also excluded were children, pregnant women, prisoners, mentally disabled, those that had received a double lung transplantation, radiation or chemotherapy of any kind within the last month and those scheduled to receive either radiation or chemotherapy.

### Recruitment strategies

Twelve medical institutions participated in the LCRT (Clinicaltrials.gov, NCT 01130285, Additional file 1: Table S1).

Participants were recruited through physician referral as well as by advertisements in local newspapers, on institutional web sites and through Clinical Trial.gov. The goal was to enroll a sample representative of the U.S. population at high risk of lung cancer death based on demographic criteria.

### Enrollment

Subjects were considered enrolled in the LCRT study when they underwent the study procedure (bronchial brush biopsy with NBEC sample collection). All enrolled subjects had a CT of the chest performed within 3 months prior to study entry or a research driven CT scan within two weeks after study entry to rule out prevalent lung cancer. Study eligibility, including smoking history, was assessed through initial contact interview by a trained clinical coordinator at each site. The initial Contact Report Form (CRF) was designed to allow for computation of number of pack-years of cigarettes smoked as well as a detailed smoking history that included information on periods of smoking cessation and use of other forms of tobacco such as pipes and cigars. The CRF also contained questions on personal history of selected diseases, stroke, and diabetes, family history of lung cancer, occupational history (jobs and industries either previously demonstrated or thought to be associated with increased risk for lung disease or lung cancer), education, and marital status.

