**Discussion:**

Over a two-year span (2010–2012), 403 subjects were enrolled at 12 sites. At baseline 384 subjects remained in study and mean age and smoking history were 62.9 years and 50.4 pack-years respectively, with 34 % current smokers. Obstructive lung disease (FEV1/FVC <0.7) was present in 157 (54 %). No severe adverse events were associated with bronchoscopic brushing. An NBEC and matched peripheral blood bio-specimen repository was established.

The demographic composition of the enrolled group is representative of the population for which the LCRT is intended. Specifically, based on baseline population characteristics we expect lung cancer incidence in this cohort to be representative of the population eligible for low-dose Computed Tomography (LDCT) lung cancer screening. Collection of NBEC by bronchial brush biopsy/bronchoscopy was safe and well-tolerated in this population. These findings support the feasibility of testing LCRT clinical utility in this prospective study. If validated, the LCRT has the potential to significantly narrow the population of individuals requiring annual low-dose helical CT screening for early detection of lung cancer and delay the onset of screening for individuals with results indicating low lung cancer risk. For these individuals, the small risk incurred by undergoing once in a lifetime bronchoscopic sample collection for LCRT may be offset by a reduction in their CT-related risks. The LCRT biospecimen repository will enable additional studies of genetic basis for COPD and/or lung cancer risk.

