### Follow up

Subjects enrolled into the study were followed at 30 days for adverse events (AE) and serious adverse events (SAE) possibly related to the study procedure and then every 3 months throughout the first two years following enrollment. A research driven CT was done at the one and two year anniversaries of enrollment if a standard of care CT was not done within three months of the anniversary. The next follow-up is planned for 2016 with another in 2018. At each follow-up subjects will receive medical record review and phone interview. Those who meet USPSTF guidelines will be encouraged to enter the closest CT screening program for early detection of lung cancer. Those who do not meet current reimbursement criteria for CT screening will receive a study driven chest CT.

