### Safety analysis: adverse events and serious adverse events

Subjects were monitored for all adverse events (AE) immediately following bronchoscopy until deemed medically stable and ready for discharge and again at 30 days after study enrollment by way of a phone call with the subject. Subjects were monitored for serious adverse events (SAE) for two years following enrollment.

Possible AEs included, but were not limited to, fatigue, muscle aches, bitter taste in mouth, dry or sore throat, hoarseness, fever [greater than 100 °F for more than 24 hours], bronchospasm, arrhythmia, pneumothorax, hemoptysis, shortness of breath and infections. A SAE was defined as any serious effect on the health or safety or any life-threatening problem or death caused by, or associated with the study procedure if that effect, problem or death was not previously identified in the investigational plan or application. These included hospitalization [≥24 hours], death, disability, or any event that require intervention to prevent damage.

AEs and SAEs were documented and classified in terms of severity [mild, moderate, severe], expectedness [expected or unexpected] and relatedness [unlikely, possibly, probably or unknown]. A medical monitor at the data coordinating center ([name] at Henry Ford Health System) worked closely with each site PI and ultimately was responsible for the final determination of SAE relatedness. Treatments or interventions and outcomes also were documented.

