### Feasibility of LCRT implementation (safety and acceptance by subjects)

The LCRT biomarker requires a one-time acquisition of NBEC through bronchial brush biopsy at the time of bronchoscopy. In addition to the LCRT study, Department of Defense Lung Cancer Research Program, and NIH recently funded other large studies assessing utility of biomarkers measured in NBEC obtained at bronchoscopy intended to more accurately determine lung cancer risk and/or to enable early lung cancer diagnosis ([name], Clinicaltrials.gov NCT01475500 CA152662 and CA102353; [name], Clinicaltrials.gov NCT02504697 DECAMP-2 and CA164783-04; [name], CA152751-05S2). Therefore, it is important to carefully evaluate the safety and comfort of this procedure, which will impact general acceptance by patients and clinicians. Based on published studies, bronchoscopy with or without biopsy is considered a safe procedure and it is used not only for medical purposes but also to conduct research [5, 41–49]. Reported complication rates (also known as serious adverse event/SAE rates) for all bronchoscopy procedures range from 0.08-1.93 % and mortality rates range from 0.004-0.045 % [50–52]. One large Japanese study of almost 50,000 patients who underwent bronchoscopy with brush biopsy in either central or peripheral airways reported a complication (SAE) rate of 0.46 %. This risk of complication is similar to the 0.28-0.32 % complication (SAE) rate reported for colonoscopy [53, 54] which is routinely used and repeated for colorectal cancer screening. Importantly, a bronchoscopy with brush biopsy limited to the *central airways* for collection of NBEC, the procedure used here, virtually eliminates risk for the primary complications reported to be associated with bronchoscopy, including pneumothorax or significant hemorrhage. Consistent with this, we observed no SAE associated with bronchoscopic brush biopsy in the subjects enrolled based on SD bronchoscopy.

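### Enrolment requires that a brush sample was collected and day-30 safety follow-up is tied to enrolment, so a study-driven bronchoscopy stopped before sampling falls outside the day-30 safety endpoint

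*Protocol article*

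**What the plan says.** Consent precedes the bronchoscopy (Participants), but enrolment comes later: "Subjects were considered enrolled in the LCRT study when they underwent the study procedure (bronchial brush biopsy with NBEC sample collection".

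The Follow up section assigns day-30 safety follow-up to that group: "Subjects enrolled into the study were followed at 30 days for adverse events (AE) and serious adverse events (SAE". The Safety analysis section times the later contacts from the same point. The day-30 contact takes place "again at 30 days after study enrollment by way of a phone call with the subject", and for serious events "Subjects were monitored for serious adverse events (SAE) for two years following enrollment". A serious adverse event must be tied to the study procedure (for example "death caused by, or associated with the study procedure"), which the Enrollment section identifies as brushing with sample collection.

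One sentence is worded more loosely: "Subjects were monitored for all adverse events (AE) immediately following bronchoscopy until deemed medically stable and ready for discharge". It does not say that these subjects had to be enrolled.

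Safety at day 30 is the first secondary endpoint (Study design), and the article presents it as reached (Background; opening of Results). For the SD group the Discussion states that "we observed no SAE associated with bronchoscopic brush biopsy in the subjects enrolled based on SD bronchoscopy". The Abstract and the Conclusions say: "Collection of NBEC by bronchial brush biopsy/bronchoscopy was safe and well-tolerated in this population".

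**The concern.** The rule that creates the analysis cohort also creates the safety population. For the biomarker question it is sensible to require a sample, since a subject without cells has no LCRT value. For the safety question the same requirement conditions on an outcome of the procedure. A consented subject whose bronchoscopy was begun and then abandoned before any cells were collected, for instance because of bronchospasm, arrhythmia or breathlessness (all on the article's own list of possible adverse events), is not enrolled. That subject is then in neither the numerator nor the denominator at day 30.

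This matters most for SD subjects. The section comparing SOC and SD characteristics says they represent people who would have bronchoscopy solely to supply the sample. For them, sedation, insertion and passage through the airway are all part of the burden of the test, and an abandoned attempt is direct evidence on tolerability. The article uses its safety result to predict that patients and clinicians will accept the procedure, so the population behind that result should be the one it speaks for.

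**Working it through.** **1. The definitions, followed for one subject.** Take a consented SD subject whose bronchoscope is inserted and withdrawn before the first brushing yields cells.
- Enrollment: not enrolled, because no brushing with collection took place.
- Follow up: the day-30 contact is for enrolled subjects, so none is specified.
- Safety analysis: the day-30 call and the two-year window have no start date for this subject. Monitoring to discharge may apply, as that sentence does not mention enrolment.

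The subject is therefore outside the day-30 endpoint. No text available to me defines a wider safety set.

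**2. The article's counts.** From Results, Enrollment: 288 SOC + 115 SD = 403, and 403 − 18 − 1 = 384. The SOC/SD comparison gives 269 + 115 = 384. Since 288 − 269 = 19, all removals were in the SOC group and the SD denominator stays at 115. The counts agree. They start from enrolment, not from attempts.

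**3. What the reported zero supports.** For 0 events in 115, the exact two-sided 95% upper limit is 1 − 0.025^(1/115) = 3.2%.

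**4. How many SD attempts could be missing.** The available text gives no count, so the stop rate f is assumed. Missing attempts = 115/(1 − f) − 115.

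| Assumed f | Missing SD attempts |
|---|---|
| 1% | 1.2 |
| 3% | 3.6 |
| 5% | 6.1 |

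**5. Effect of one serious event among them** (exact Clopper-Pearson limits).

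| Stopped attempts added | Result | 95% CI |
|---|---|---|
| none | 0/115 = 0% | 0 to 3.2% |
| 1, with one event | 1/116 = 0.86% | 0.02% to 4.7% |
| 6, with one event | 1/121 = 0.83% | 0.02% to 4.5% |

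**6. Against the comparator.** The Discussion cites 0.28–0.32% for colonoscopy. That range lies inside every interval in step 5, so one uncounted event would remove the statement of no serious events without establishing a rate different from the comparator. Equally, at a true rate of 0.32% the chance of no event in 115 subjects is (1 − 0.0032)^115 = 69%, so the zero is weak evidence to begin with.

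**The case against.** **No stopped procedure is shown.** This stands. Fig. 1 and part of the Results were not available to me, and either could hold a count of attempts. The point concerns whom the stated rule leaves out; it is not evidence that anyone was left out.

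**The full investigational plan may define a separate safety set.** Possible, and an article need not repeat such detail. But this article states both the enrolment rule and the population followed at day 30, and together they give the result described.

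**A reader might infer that stopped subjects had no safety monitoring.** The documents do not support that. Monitoring up to discharge is described for subjects without reference to enrolment. Nor do they show that events arising during bronchoscopy fall outside the monitoring window: the wording on timing can be read that way, but nothing excludes such events and the list of possible adverse events is open-ended.

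**A reader might infer that only fully completed procedures count, so that completion is 100% by definition.** That is also too strong. Sample collection describes 5 to 10 repeated passes, and a procedure stopped after an early pass that yielded cells need not prevent enrolment. Moreover, matched blood and NBEC are reported for 361 of 384 subjects, without saying which sample the other 23 lacked. If some lacked NBEC, the rule was not strictly applied.

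**The serious-event claims concern brushing, and most subjects were SOC.** Largely fair. In SOC subjects brushing followed the diagnostic work, so an earlier stop is mainly an event of clinical care. The assumed stop rate should therefore not be applied to all 403. The argument rests on the SD group, and on the Abstract and Conclusions, whose wording extends to bronchoscopy and to tolerability.

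**Conclusion.** The point holds in a limited form. By the article's own definitions, the day-30 safety population is selected on a sample having been obtained, and an SD bronchoscopy stopped before that is not counted in the first secondary endpoint. The conclusion on safety and tolerability is broader than that population.

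The size and even the existence of actual bias are unknown. The figure of 1 to 6 missing SD attempts rests on an assumed stop rate of 1% to 5%, and the change from 0/115 to about 1/116 needs the further assumption of one serious event among them. Even then the interval includes the colonoscopy comparator. A reader should not infer that the reported safety result is wrong or that the procedure is less safe than stated; the documents support neither. The primary endpoint and the LCRT accuracy analyses are unaffected.

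**What to change.** Define the safety set separately from the LCRT cohort: every consented subject in whom a study-driven bronchoscopy was started, plus every standard-of-care subject in whom research brushing was attempted. From existing consent and procedure logs and charts at the 12 sites, report attempted, completed and stopped procedures with reasons, and events to day 30, separately for SD and SOC. Keep the 384 for all LCRT analyses. If counts of attempts are already held, use them as the denominator.

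If the logs cannot be recovered, limit the safety conclusion in the Abstract, the Discussion section on feasibility of implementation, and the Conclusions to subjects in whom brushing with sample collection was performed.

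The cost is a small retrospective query, some chart review and revised wording, with no new subjects, visits or procedures. The downside is that the safety figure may become less favourable.

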### Sample collection

Standardized sample collection kits were provided to each site. Kits contained supplies for the collection and labeling of biological samples including a disposable bronchial cytology brush (ConMed Corporation, Utica, NY ref.#149) for the collection of NBEC, a 10 ml K_2_-EDTA vacutainer tube (Becton, Dickinson and Company, Franklin Lakes, NJ ref.#366643) for the collection of whole blood and barcoded stickers. Following positioning of the bronchoscope, the cytology brush was inserted and NBEC were collected from a grossly normal region of either main stem bronchus. For SOC bronchoscopies, this occurred immediately after the diagnostic procedures on the opposite side or in a separate area from the lung region under clinical investigation. If the patient had received a lung transplant, the specimen was obtained from the recipient native mainstem bronchus. The brush was withdrawn, shaken into a tube of normal saline chilled on ice and re-inserted into the bronchoscope for collection of additional NBEC. This procedure was repeated a total of 5–10 times. After the last brushing, the cytology brush was shaken in the saline and then dabbed onto a glass slide to enable assessment by a pathologist. Immediately prior to or immediately following bronchoscopy, approximately 10 ml of whole blood was obtained using standard phlebotomy techniques into a K_2_-EDTA vacutainer tube. Blood and NBEC samples were transferred to the lab within 10 min. for processing and stabilization, which was initiated within 1 hour post-collection.

### Follow up

Subjects enrolled into the study were followed at 30 days for adverse events (AE) and serious adverse events (SAE) possibly related to the study procedure and then every 3 months throughout the first two years following enrollment. A research driven CT was done at the one and two year anniversaries of enrollment if a standard of care CT was not done within three months of the anniversary. The next follow-up is planned for 2016 with another in 2018. At each follow-up subjects will receive medical record review and phone interview. Those who meet USPSTF guidelines will be encouraged to enter the closest CT screening program for early detection of lung cancer. Those who do not meet current reimbursement criteria for CT screening will receive a study driven chest CT.

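### The safety text is inconsistent on whether relatedness is a condition for recording a serious event or a later classification, so the zero-SAE conclusion is partly built into the SAE definition

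*Protocol article*

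**What the plan says.** Two Methods sections of the protocol article describe safety ascertainment.

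- **Follow up.** Subjects were "followed at 30 days for adverse events (AE) and serious adverse events (SAE) possibly related to the study procedure", and then contacted every three months for two years.
- **Safety analysis, scope.** "Subjects were monitored for all adverse events (AE) immediately following bronchoscopy until deemed medically stable and ready for discharge and again at 30 days", the latter by telephone. For serious events: "Subjects were monitored for serious adverse events (SAE) for two years following enrollment".
- **Safety analysis, definition.** A death, a life-threatening problem or a serious effect counts as an SAE when it is "caused by, or associated with the study procedure if that effect, problem or death was not previously identified in the investigational plan or application". The next sentence names the kinds of event included: hospitalization of at least 24 hours, death, disability, and events needing intervention to prevent damage.
- **Safety analysis, classification.** AEs and SAEs were then graded for severity, for "expectedness [expected or unexpected"], and for "relatedness [unlikely, possibly, probably or unknown"]. The medical monitor worked with each site's principal investigator and "ultimately was responsible for the final determination of SAE relatedness".

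Safety at day 30 is a secondary endpoint (Study design). The Abstract reports no severe events associated with the brushing. The Discussion (Feasibility of LCRT implementation) reports no associated SAEs in either the standard-of-care or the study-driven group, and describes the event rate as much lower than that of screening colonoscopy.

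**The concern.** A safety count can be read only if the reader knows what was eligible to enter it. The usual order is to record every event that meets a seriousness criterion, then rate cause and expectedness. Here the two ratings also appear inside the definition, and the two sections give different scopes for the 30-day contact.

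If sites followed the definition as written, someone had to judge association, and whether the event was already listed, before the event could become an SAE for the monitor to rule on. The statement that no SAE was associated with brushing would then reflect the entry rule as well as what happened to subjects. That statement supports the claim that the procedure is safe in people with COPD, interstitial lung disease or a transplanted lung, and the argument that it will be acceptable to patients and clinicians.

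**Working it through.** No figure in the plan depends on this wording, so the check sets the sentences side by side.

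**Step 1: scope at 30 days.** Follow up restricts AEs and SAEs to those that might be related. The safety section says all AEs. Both describe the same contact. Follow up does not say who judges possible relatedness or when.

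**Step 2: what the literal definition admits.** It has two conditions beyond seriousness: association with the procedure, and absence from the investigational plan or application.

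| Serious event, as judged at the site | Not listed in plan | Already listed in plan |
|---|---|---|
| Associated with procedure | SAE | not an SAE |
| Not associated | not an SAE | not an SAE |

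One of four cells qualifies. One could instead parse the sentence so that the causal phrase governs only life-threatening problems and deaths. The novelty condition would still apply to all three kinds of outcome, because it names effect, problem and death.

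**Step 3: compare with the classification.** Four relatedness levels times two expectedness levels give 4 × 2 = 8 possible ratings of an SAE. I take expected to mean previously identified in the plan, which is an assumption.

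- The 4 expected ratings conflict with the novelty condition.
- Unlikely and unexpected (1 rating) conflicts with the association condition.
- Possibly and unexpected, and probably and unexpected, fit (2 ratings).
- Unknown and unexpected (1 rating) is undetermined.

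So 5 of the 8 ratings should be empty if the definition is applied. The definition and the grading cannot both be followed as written.

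**Step 4: an example.** Take a hospital admission for infection on day 10. Infections are among the possible AEs listed in the safety section, so under that section the 30-day call should capture it as an AE. It is an SAE only if judged associated and not already listed. If infection is also listed in the plan or application (an assumption), even an admission judged related fails the definition. After day 30 the safety section monitors only SAEs, so a serious event outside the definition has no stated AE route into the record.

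**Step 5: scale.** The inputs are 403 enrolled and brushed, 384 retained (Enrollment), and cited complication rates of 0.28-0.32% for colonoscopy and 0.46% for bronchoscopy with brush biopsy (Discussion).

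- One event: 1/403 = 0.25%, or 1/384 = 0.26%.
- Events expected at the colonoscopy rates: 403 × 0.0028 = 1.13 to 403 × 0.0032 = 1.29.
- Events expected at the brush-biopsy rate: 403 × 0.0046 = 1.85.

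The comparison therefore turns on one or two events. This shows how sensitive the claim is to the entry rule. It does not estimate how many events were left out.

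**The case against.** The strongest reply is that the safety section, which is the dedicated one, says all AEs were monitored to discharge and again at 30 days. Its unlikely and unknown categories would serve no purpose if only related events were written down. The phrase in Follow up may simply state the purpose of the call. This stands. A reader might infer that sites collected only events they already considered related, and the documents do not support that.

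A reader might also infer that no all-cause count exists, or that the monitor rated events down. Neither can be asserted. Part of the Results was not available for this review and may contain the safety counts, and nothing says in which direction the monitor's decisions went. Having one central monitor, based at a participating institution, is a design choice and contradicts nothing.

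Background deaths over two years would be a poor measure of the problem. The endpoint is at day 30, and background mortality is not the same as missed procedure-related events.

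Finally, accrual ended in March 2012, so new wording cannot change what was collected. That limits the remedy for past events, but not the need to state which rule was applied.

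The reply does not remove the contradiction within the SAE definition. Recording all AEs does not make an excluded serious event an SAE, and the text gives the monitor the decision on SAE relatedness only.

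**Conclusion.** The text is wrong as written on two counts. The two sections disagree on the scope of the 30-day contact. The SAE definition makes relatedness and novelty entry conditions that the same section then treats as later ratings. Applied literally, the definition keeps serious events judged unrelated, and related serious events already listed, out of the count behind the zero-SAE conclusion.

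The effect on results is not demonstrated. The tempting conclusion that the zero is an artefact goes beyond the documents: no missed event is shown, and the number of serious events before adjudication is not in the text available. The sensitivity is clear, however, since one event in 403 would be 0.25%, close to the colonoscopy figures used for comparison. The point rests on reading the definition as worded and on taking expected to mean previously identified. If sites in practice reported every serious event and rated it afterwards, the correction is one of wording only.

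**What to change.** 1. Reconcile Follow up with the safety section, so that the 30-day contact has one stated scope.
2. Define an SAE by seriousness alone, using the kinds of event the section already names: death, hospitalization, disability, and intervention to prevent damage. Assign relatedness and expectedness afterwards.
3. Report all-cause serious events to day 30 and to two years beside the procedure-associated count. Show events of unknown relatedness in their own row. Counting them all as associated would charge complications of the diagnostic procedures in standard-of-care subjects to the brushing, and leaving them out would do the reverse.
4. State which rule the sites applied. If it was the literal definition, check for omitted events in records already held and in the medical record review planned for 2016. Otherwise qualify the zero-SAE statement and the colonoscopy comparison.

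The first three steps cost some wording and one table. The fourth costs more: it looks back to 2010-2012 at 12 sites, and the plan expects about 20% of subjects not to be re-contacted, so recovery may be incomplete. The price is a longer event listing and possibly a less favourable safety statement.
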